**Methodology**

*Objective*

To examine differences in organ failure that develop in patients who have fatal anaphylaxis after being exposed to different allergen trigger categories.

*Primary Question*

Is allergen exposure category associated with the type of organ failure that subsequently develops in fatal anaphylaxis?

*Design, Setting and Participants*

This is a population based retrospective analysis of consecutive anaphylaxis deaths of all ages in Australia between 1^st^ January 2003 and 31^st^ December 2022.

*Outcome*

Development of primary organ failure being either due to: Upper airway oedema, Bronchospasm (lower respiratory obstruction), Cardiovascular.

*Exposure*

Patient allergen exposure to one of 4 categories of allergens: Drug; Insect; Food; and Radiology Contrast.

*Covariates*

Covariates collected are Age, pre-existing history of asthma, pre-existing atopic disease, previously allergic to allergen, American Society of Anaesthesia Physical Status score, use of antihypertensives.

*Other variables*

A broad range of variables have been defined (Table 1 and 2) prior to data collection and may be used as covariates – see below

*Ethical Approval*

Approval was obtained from the University of Melbourne Research Ethic Committee, the Victorian Department of Justice Human Research Ethics Committees and the Coroners Court of Victoria Research Committee.

**Data Collection and Management**

*NCIS Case identification*

The NCIS allows for identification of anaphylaxis cases through 3 fields: cause of death free text fields; ICD 10 (coded externally through linkage to the Australian Bureau of Statistics); search of keywords in attached reports. The search strategy for this study is:

1. Cause of death field search using search term “anaphyl*” in all primary and antecedent causes of death listed
2. ICD 10 search
   1. T78 Anaphylaxis (includes food)
   2. T805 Serum Anaphylaxis
   3. T886 Anaphylaxis to drug correctly administered
   4. T634 Arthropod Anaphylaxis
   5. Y575 Drug anaphylaxis
3. Keyword search function of reports
   1. Anaphyl*

We will not separately screen asthma cases for anaphylaxis because a previous NCIS study only found 1 case out 1978 asthma deaths did not have anaphylaxis listed as an antecedent cause.^16^

*Case Screening and Inclusion*

Cases will be screened for inclusion by two critical care physicians who are trained in anaphylaxis case identification independently.

Where there is doubt about the diagnosis of anaphylaxis for inclusion expressed by either physician, cases will be referred to a specialist in Allergy and Immunology for final determination regarding inclusion. Cases identified and those excluded with reasons will be collected on an excel spreadsheet.

*Data Collection*

Study data will be collected and managed using REDCap electronic data capture tools hosted at University of Melbourne. REDCap (Research Electronic Data Capture) is a secure, web-based software platform designed to support data capture for research studies.

Data from each case will be extracted by two critical care clinicians independently. Using the REDCap data comparison tool, any differences will be resolved through agreement and where agreement cannot be reached, the case will be discussed with an expert panel incorporating Anaesthesia, Allergy and Immunology and Primary Care who are part of the study group.

*Data Variables*

Identification of Organ Failure

Instructions for allocation of organ failure were derived from agreement of the expert panel of authors incorporating the specialties of Anaesthesia, Emergency Medicine, Allergy and Clinical Immunology, and Primary Care. The panel used a three step process to develop descriptors of organ involvement. The first was mapping descriptors from nine grading systems identifying symptoms of anaphylaxis and two organ specific (asthma and laryngotracheobronchitis severity descriptors) to categorise them as signifying upper airway, lower airway (bronchospasm) and cardiovascular compromise. The second step involved refining criteria with regard to potential overlap of symptoms/signs including consideration of published data as described above in the background section on organ failure interrelation and overlap of symptoms. The third step was revision from individual domains of expertise from each specialty.

The nine acute allergy grading systems and two organ specific severity guides that covered both adult and paediatric anaphylaxis were mapped to extract symptoms of upper airway, lower respiratory obstruction and cardiovascular symptoms to be identified in the immediate lead up to cardiorespiratory arrest in each case.

- One international allergist based system^19^
- One Delphi study designed for all setting and triggers^7^
- One retrospective ED observation study 30% insects, 22% drugs, 18% food^3^
- One published proposal for universal grading (expert opinion)^20^
- Two grading systems designed for drugs^9, 21^
- Three grading systems designed for allergist food trials^22-24^
- One grading system for insect anaphylaxis^25^
- Two clinical practice guidelines for other conditions with single organ involvement^26, 27^

Once organ involvement was deemed to present the data extractors were required to use clinical assessment as to which organ failure contributed to deterioration prior to cardiac arrest.

When more than one organ failure type was deemed to be present then the data extractors were required to agree on the organ failure that predominantly led to cardiorespiratory arrest. Secondary organ failure was also recorded. The American Society of Anaesthesiologists (ASA) Physical Status Classification System^16^ was used to estimate comorbidities for each case. Other variables collected include age, sex, allergen trigger, pre-existing asthma status, physical location of reaction in relation to healthcare, time from allergen exposure to symptoms, time to severe symptoms, time to cardiorespiratory arrest, whether the patient was administered adrenaline before collapse, intubation status, presence of vomiting or aspiration clinically or on autopsy, whether the patient survived initial resuscitation longer than 2 hours, and the number of days to death if initial survival occurred.

Table 1 contains the data definitions and derivation for complex variables requiring clinical interpretation.

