Most series reported respiratory symptoms as a composite of airway oedema and bronchospasm and only three authors separated respiratory components. The predominant organ systems failure or sequence of organ failure was only reported by two authors. Cardiovascular failure ranged from 12% to 100%. Respiratory failure was present in most cases ranging from 53% to 100%. Food related fatalities were children and young adults who died predominantly from respiratory failure with a high frequency of bronchospasm reported (75%). Venom series were older with a very high frequency of cardiovascular collapse (59% to 81%) and lower frequency of respiratory involvement (19% to 53%) which was predominantly upper airway failure when present. Drug related fatalities had high frequencies of both cardiovascular (47% to 100%) and respiratory (60% to 74%) failure.

*Australian National Coronial Information System*

In Australia each state and territory jurisdiction legislates that any unexpected death is reported to the state Coroner, including those that occur in healthcare. The coroner’s role is to establish the cause of death and circumstances through collation of eye witness statements and medical records as well as autopsy. For each reported death the coroner produces formal written findings. The National Coronial Information System contains all deaths reported to state coroners and includes documents that include the formal findings, the police report containing any eyewitness accounts of events surrounding the death, toxicology reports and formal autopsy findings with case synthesis.

Anaphylaxis deaths are all unexpected and are thus reported to state coroners and contained within the NCIS. However, there are some cases where coronial notification is not made and a death certificate is written by medical practitioners without coronial involvement. This occurs where circumstances and cause of death are clear and the requirement for notification is interpreted differently by individual medical practitioners. In a previous anaphylaxis study by Mullins et al comparing national death certificates through the Australian Bureau of statistics and NCIS case reports between 2000 and 2013, 223 out of 298 were recorded in the NCIS.^16^ It is not possible to determine which cases are not reported to state coroners. Despite this missing data, NCIS cases can be considered to be representative of a whole population.

*Cohort Studies*

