**ORGAN FAILIRE TYPES**

- 1. **Upper Airway Oedema present**

| **Definition** | Upper Airway Oedema present during the anaphylaxis episode | | |
| --- | --- | --- | --- |
| **Data name** | Airway Oedema | **Collection** | Manual extraction |
| **Data Type** | Single answer | **Date Started** | 01/05/2024 |
| **Field Size** | Drop down yes/no/not recorded | **Layout** |  |
| **Code Set** | [airway_oedema] = '1' |  |  |
| **Reporting guide** | Yes if ANY of the following present   - Stridor - Altered voice - Tongue/oropharyngeal swelling - Obvious laryngeal swelling at 1^st^ laryngoscopy - Gross macroscopic laryngeal swelling at autopsy | | |
| **Purpose and basis for reporting guide** | To objectively determine presence of upper airway oedema during the anaphylactic reaction that contributed to death.  Criteria developed on expert consensus with consideration of upper respiratory descriptors in published grading systems^3, 7, 21, 30^. Laryngeal swelling may occur after multiple laryngoscopy attempts^1^ – first laryngoscopy and autopsy findings have been qualified to take this confounding element into consideration. Number of laryngoscopy attempts is recorded during data extraction. | | |
| **Outcome #** | **Outcome Text Label** | **Outcome Code Set** | **Definition Note** |
| 1 | Yes |  |  |
| 2 | No |  |  |
| 3 | Not recorded |  | Presence **OR** Absence of symptoms **not** recorded |

- 1. **Bronchospasm present**

| **Definition** | Bronchospasm present during anaphylaxis episode | | |
| --- | --- | --- | --- |
| **Data name** |  | **Collection** | Manual extraction |
| **Data Type** |  | **Date Started** | 01/05/2024 |
| **Field Size** | Drop down yes/no/not recorded | **Layout** |  |
| **Code Set** | [bronchospasm] = 1 |  |  |
| **Reporting guide** | Yes if ANY of the following present   - Persistent cough - Wheeze - Chest tightness with history of asthma - Dyspnoea with history of asthma - Cyanosis or hypoxia <93% with history of asthma (excluding isolated upper airway obstruction) - Cyanosis hypoxia <93% without documented or clinical hypotension - Increased work of breathing (excluding isolated upper airway obstruction) - Patient’s usual asthma symptoms - Bronchodilator use during episode - High peak inspiratory pressure in intubated patient (subjective or greater than 30cm H2O) - Difficult to ventilate - Upsloping CO2 trace or obstructive airway pattern | | |

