| **Reporting guide** | This is the organ failure type that predominates the reaction – specifically which is most severe.  However if two organ failure elements cannot be delineated between primary and secondary, then the organ with symptoms that were most pronounced first in time should be listed as the primary organ failure type.  A cardiorespiratory arrest that occurs with upper airway oedema or bronchospasm present in isolation should NOT have cardiovascular reaction present after the arrest unless there is prolonged requirement for vasopressor support. | | |
| **Purpose and rationale** | To record the predominant organ failure type leading to cardiorespiratory arrest. | | |
| **Outcome #** | **Outcome Text Label** | **Outcome Text Label** | **Definition Note** |
| 1 | Airway Oedema |  | A cardiorespiratory arrest that occurs predominantly from upper airway oedema symptoms |
| 2 | Bronchospasm |  | A cardiorespiratory arrest that occurs predominantly from bronchospasm symptoms |
| 3 | Cardiovascular |  | A cardiorespiratory arrest that occurs predominantly from cardiovascular symptoms |
| 4 | Pulmonary oedema |  | A cardiorespiratory arrest that occurs predominantly from pulmonary oedema symptoms |
| 5 | Unable to determine |  | Insufficient information to comment. |

- 1. **Secondary Organ Failure Type**

| **Definition** | The organ involvement that was present and contributed less to the cardiorespiratory arrest than the primary organ failure type involved. | | |
| --- | --- | --- | --- |
| **Data name** | secondary_organ_failure | **Collection** | Manual |
| **Data Type** | Dropdown | **Form** |  |
| **Field Size** | 1-5 see below | **Layout** |  |
| **Reporting guide** | This is the organ failure type that was present during the anaphylaxis reaction but was not the primary reason for cardiorespiratory arrest; or was the reaction that occurred second in time if considered equal in magnitude to the primary mechanism.  Example – Upper airway oedema that was observed on laryngoscopy.  in a bronchospasm primary organ failure patient | | |
| **Purpose and rationale** | To record the predominant organ failure type leading to cardiorespiratory arrest. | | |
| **Outcome #** | **Outcome Text Label** | **Outcome Text Label** | **Definition Note** |
| 1 | Airway Oedema |  | A cardiorespiratory arrest that occurs predominantly from upper airway oedema symptoms |

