| radio | ASA Status  ASA 1  Healthy Patient  ASA2  Mild diseases only without substantive functional limitations. Current smoker, social alcohol drinker, pregnancy, obesity (30<BMI< 40), well-controlled DM/HTN, mild lung , Asymptomatic congenital cardiac disease, well controlled dysrhythmias, asthma without exacerbation, well controlled epilepsy, non-insulin dependent diabetes mellitus, abnormal BMI percentile for age, mild/moderate OSA, oncologic state in remission  ASA3  Substantive functional limitations; One or more moderate to severe diseases. Poorly controlled DM or HTN, COPD, morbid obesity (BMI ≥40), active hepatitis, alcohol dependence or abuse, implanted pacemaker, moderate reduction of ejection fraction, ESRD undergoing regularly scheduled dialysis, history (>3 months) of MI, CVA, TIA, or CAD/stents. Uncorrected stable congenital cardiac abnormality, asthma with exacerbation, poorly controlled epilepsy, insulin dependent diabetes mellitus, morbid obesity, malnutrition, severe OSA, oncologic state, renal failure, muscular dystrophy, cystic fibrosis, history of organ transplantation.  ASA4  Recent (< 3 months) MI, CVA, TIA or CAD/stents, ongoing cardiac ischemia or severe valve dysfunction, severe reduction of ejection fraction, shock, sepsis, DIC, ARD or ESRD not undergoing regularly scheduled dialysis. Symptomatic congenital cardiac abnormality, congestive heart failure, active sequelae of prematurity, acute hypoxic-ischemic encephalopathy, shock, sepsis, disseminated intravascular coagulation, automatic implantable cardioverter-defibrillator, ventilator dependence, endocrinopathy, severe trauma, severe respiratory distress, advanced oncologic state. | 1, 1 \| 2, 2 \| 3, 3 \| 4, 4 |
| radio | Trigger | 1, Food \| 2, Medication \| 4, Immunotherapy/Allergy Testing \| 5, Radiology Contrast \| 6, Venom \| 7, Other substance \| 8, Unable to be determined/idiopathic \| 9, Not recorded |
| radio | Previously diagnosed or documented to be allergic to this allergen? | 1, Yes \| 2, No \| 3, Not recorded |
| text | Unable to be determined/idiopathic - specify details |  |
| text | Other substance specify agent/allergen and route |  |
| radio | Insect Venom Type | 1, Bee \| 2, Wasp \| 3, Ant \| 4, Tick \| 5, Unknown |
| text | Insect further details - eg how many stings, circumstances |  |
| text | Radiology Contrast Specify Agent and Route |  |

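### In deaths with more than one organ type present, the primary outcome is a judgement of which organ predominated, no masking to the allergen is described, and no planned analysis tests how far the association depends on that judgement

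*Combined protocol and SAP*

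**What the plan says.** In the protocol, under Data Collection and Management (identification of organ failure), organ involvement is first established, and then "the data extractors were required to use clinical assessment as to which organ failure contributed to deterioration prior to cardiac arrest". When more than one type is present, "the data extractors were required to agree on the organ failure that predominantly led to cardiorespiratory arrest". Table 1, Primary Organ Failure Type, adds: "This is the organ failure type that predominates the reaction – specifically which is most severe". It gives no scoring rule for severity. If two types cannot be separated, "the organ with symptoms that were most pronounced first in time should be listed as the primary organ failure type".

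The safeguard is duplicate work: "Data from each case will be extracted by two critical care clinicians independently". Differences are settled by agreement and, failing that, by an expert panel drawn from the study group. The protocol mentions neither masking to the allergen nor an agreement statistic. In Table 2 the trigger field comes before the organ fields in a single variable list, next to an item that requires the allergen to be known: "Previously diagnosed or documented to be allergic to this allergen".

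Table 1 also defines three separate fields, for airway oedema, bronchospasm and cardiovascular reaction. Each is answered yes, no or not recorded against listed criteria ("Yes if ANY of the following present").

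The SAP's Primary Analysis models only the judged primary organ failure, in three logistic models. Its sensitivity analyses are multiple imputation (if more than 10% of data are missing) and the unadjusted odds ratio. Its subgroups are by age. None uses the three organ fields.

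**The concern.** The exposure is the allergen and the outcome is a reader's call, so the two should be ascertained separately or the dependence examined. Here the readers also record the trigger, and the protocol's background tells them what earlier series found: "Food related fatalities were children and young adults who died predominantly from respiratory failure with a high frequency of bronchospasm reported" (75%), and cardiovascular collapse in 59% to 81% of venom deaths. If a mixed respiratory and cardiovascular picture is resolved towards the expected organ for that allergen, the error differs by exposure group and moves the odds ratios away from 1 in the expected direction. Two readers with the same expectation can agree and still share the error.

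At stake is the study's central association, which the SAP describes as a causal effect. The protocol also faults the one earlier series that reported organ failure as an explicit outcome for not describing its allocation method. How robust the allocation is therefore bears on what this study adds.

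**Working it through.** **Where judgement enters.** The choice of a predominant organ arises only when at least two types are present. The documents do not count such deaths or tabulate the three organ fields by allergen. The share of outcomes exposed to the choice is therefore unknown, and the proposed checks cannot be computed from the documents. What can be computed is how many changed calls would matter.

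**Inputs** (complete-case counts, Tables S2a and S2b). Cardiovascular: insect 21/37, drug 40/115. Bronchospasm: insect 9/37, food 55/58, drug 68/115.

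**Formula.** With a events and b non-events in the named group, and c and d in the drug group: OR = ad/(bc); SE of log OR = √(1/a + 1/b + 1/c + 1/d); 95% CI = exp(log OR ± 1.96 SE).

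**Reproducing the published crude values**
- Cardiovascular, insect v drug: (21×75)/(16×40) = 1575/640 = 2.461; SE = √(1/21 + 1/16 + 1/40 + 1/75) = 0.385; CI 1.156 to 5.237.
- Bronchospasm, insect v drug: (9×47)/(28×68) = 423/1904 = 0.222; CI 0.096 to 0.514.
- Bronchospasm, food v drug: (55×47)/(3×68) = 2585/204 = 12.672; CI 3.741 to 42.924.

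All three match Tables S2a and S2b to three decimals.

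**Changing k calls in the named group, with drug left as published**

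| Contrast | k | Odds ratio | 95% CI |
| --- | --- | --- | --- |
| Cardiovascular, insect v drug | 1 of 21 | (20×75)/(17×40) = 2.206 | 1.040 to 4.679 |
| | 2 of 21 | (19×75)/(18×40) = 1.979 | 0.935 to 4.191 |
| Bronchospasm, insect v drug (cardiovascular calls moved to bronchospasm) | 5 | (14×47)/(23×68) = 0.421 | 0.196 to 0.901 |
| | 6 | (15×47)/(22×68) = 0.471 | 0.222 to 1.002 |
| Bronchospasm, food v drug | 11 of 55 | (44×47)/(14×68) = 2.172 | 1.071 to 4.405 |
| | 12 of 55 | (43×47)/(15×68) = 1.981 | 0.988 to 3.972 |

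**Limits of this arithmetic.** It is crude and one-sided: only one group is altered, always towards the null. The same exercise on the adjusted estimates needs individual data. Adjusted complete-case values are 2.920 (1.208 to 7.055) for cardiovascular and 0.178 (0.071 to 0.448) for bronchospasm, insect v drug. For bronchospasm, food v drug, the adjusted interval already includes 1: 1.980 (0.653 to 6.008).

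**How objective the organ fields are.** Of the seven cardiovascular criteria in Table 1, six require the absence of severe respiratory symptoms; only ongoing vasopressor need stands without that condition. Of the twelve bronchospasm criteria, three require a history of asthma and a fourth refers to the patient's usual asthma symptoms. The fields replace the choice between organs with explicit lists, but they do not remove judgement.

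**The case against.** The outcome is not free judgement. Descriptors were mapped from nine grading systems and two organ-specific guides and then refined by a multispecialty panel. Extraction is independent and duplicated, disputes go to the panel, and ties have a rule. All of this stands, and it answers random disagreement. It does not answer an expectation held by both readers and the panel.

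A reader might infer that expectation produced the reported pattern. The documents do not support that. Agreement with earlier series is equally what a true association would give, and the insect cardiovascular share, 56.8%, lies below the 59% to 81% that the background quotes for cardiovascular collapse. Nor do the documents state that extractors knew the allergen; it is a strong inference from the shared record and variable list.

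The insect cardiovascular contrast is the most fragile of the three examined. Even there, two changed calls leave an odds ratio near 2 in the same direction, and the SAP says it will read magnitudes and intervals rather than p-values. That is right: the interval reaching 1 marks fragility and does not reverse a finding.

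The remedy also has limits. The same extractors completed the organ fields, presence is not predominance, and restricting to single-organ deaths selects on something that happens after exposure. These limits make the checks partial. They do not make them uninformative, because each replaces the which-predominated choice with listed criteria.

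**Conclusion.** The point holds as a gap in the sensitivity analyses, not as evidence of bias. In multi-organ deaths the primary outcome depends on a predominance call by readers who very probably knew the allergen, and no planned analysis shows whether the association survives without that call.

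The size differs by contrast. In crude data, 2 changed insect calls bring 1 into the cardiovascular interval (2.46 to 1.98), whereas the bronchospasm contrasts need about 6 insect or 12 food calls. These figures assume that only the named group is altered, and they do not carry over to the adjusted estimates. The true exposure to the problem depends on the number of multi-organ deaths, which is not given.

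The checks use fields already collected and leave the primary analysis unchanged, so they are a cheap improvement that could equally well strengthen the findings.

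**What to change.** Add two analyses and report them beside the primary result:

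1. Refit the primary models with each organ field (airway oedema, bronchospasm, cardiovascular; yes v no) as the outcome. State a rule for not recorded. Label the result as presence rather than predominance: it is a different estimand, and one death can count under more than one organ.
2. Separately, refit the models in deaths where exactly one organ field is yes, again with a stated rule for not recorded, so that no predominance choice is needed. Do not pool in multi-organ deaths on which both extractors agreed, since agreement does not test a shared expectation. Report how many deaths are single-organ and multi-organ in each allergen group, subject to the rule against reporting counts below five.

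State whether extractors were masked to the allergen. Report agreement before discussion only if the independent entries were kept; the protocol describes a comparison tool for resolving differences but does not say that they were. Because Tables S2 to S4 already give results, anything added now should be labelled post hoc.

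The cost is analyst time, with no new extraction. The second analysis will have fewer deaths and sparser cells: food already has 0/58 cardiovascular deaths, and its contrasts cannot be estimated. It also selects on a post-exposure variable. The report should say that both checks are partial, because the same extractors filled in the fields, most cardiovascular criteria depend on judging respiratory symptoms not to be severe, and several bronchospasm criteria depend on asthma history.
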